## Abstract

**Background:**

The announcement of a national lockdown in South Africa had country-wide impact on the delivery of health services. Strategies included prioritisation of patients and protecting patients who were considered at risk, resulting in the need for cancellation and temporary termination of many outpatient therapy services. This necessitated the urgent need to come up with a way of delivering physiotherapy rehabilitation services to patients in a more non-traditional format. Telerehabilitation allows for the provision of services by using electronic communication, thus ensuring that patients are still able to access necessary rehabilitation services.

**Methods/design:**

This is a prospective, mixed method study with participants recruited from the outpatient physiotherapy department of Chris Hani Baragwanath Academic Hospital (CHBAH). Telerehabilitation services will be provided via the patients’ preferred method of communication. On discharge, participants and therapists will be asked about their experiences of telerehabilitation.

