At subsequent telerehabilitation sessions (scheduled approximately 3–4 weeks apart), the therapist will obtain feedback on the patient’s functional status at home by using the subjective assessment framework. Follow-up sessions will consist of a re-assessment, patient education including pain management principles, medication adherence, importance of rehabilitation, ensuring that contraindications and precautions are understood and adhered to and scar management. Patient safety will also be addressed by giving suitable advice. Exercises will be prescribed, revised and progressed as required, and patients’ concerns will be addressed. Participant compliance will be monitored by encouraging the patient to keep a rehabilitation diary in which they record their exercises and progress as well as by corroborating the information with the family member. Weekly reminders will be sent, encouraging the patient to continue with their exercise programmes. Once patients have reached their functional goal, they can be discharged.

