At each follow-up session, the following will be obtained: feedback from the caregiver on the patient’s functional status, the response of the child to the HEP and feedback/concerns from the caregiver, by using the Subjective Assessment Framework. Based on the caregiver’s report, the HEP and advice will be progressed accordingly and referrals made. At the final consultation as determined by the condition of the patient, caregivers will be requested to provide feedback on their perceptions and experiences of telerehabilitation (Appendix 5). If less than satisfactory outcome with telerehabilitation is received, face-to-face sessions will be considered as an alternative to telerehabilitation. Once patients have reached their functional goal, they can be discharged. Feedback from the therapist on the telerehabilitation experience will be collected as shown in Appendix 6.

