Frequencies and proportions will be used to summarise categorical variables. The two samples proportions test will be used to compare if there are any differences between the Yes or No responses. Comparisons between proportions with categorical variables will be performed by using the Chi squared test with the condition that the assumption is met:

5.Qualitative information will be gathered from two sources. The therapist’s experiences will be collected as positive, negative, challenges and other, and if further subthemes emerge from those categories, it will be described verbatim. In the subjective framework of questions, patients are asked a directed open-ended question on their experience of the call and the telerehabilitation sessions. The responses will also be categorised into themes that emerge.

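### The structured experience assessment is timed at discharge or the final consultation, with none described at withdrawal or early recall, so reported satisfaction may be overstated

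*Protocol article*

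**What the plan says.** All references are to the protocol article.

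- **Timing, all groups.** Abstract, Methods/design: "On discharge, participants and therapists will be asked about their experiences of telerehabilitation".
- **Timing, paediatrics.** Paediatric Procedures: "At the final consultation as determined by the condition of the patient, caregivers will be requested to provide feedback on their perceptions and experiences". The instrument is the Appendix 5 questionnaire, in which nine of the ten items offer Yes, No or N/A.
- **Discharge.** The arthroplasty and paediatric procedures use the same criterion: "Once patients have reached their functional goal, they can be discharged". The low back pain procedures allow discharge once the Keele STarT Back score is below three.
- **Leaving earlier.** High-risk back-pain patients are recalled for a face-to-face consultation after the first telerehabilitation session (low back pain Procedures). Any participant may withdraw at any time without a reason (Ethical considerations). For children: "If less than satisfactory outcome with telerehabilitation is received, face-to-face sessions will be considered as an alternative to telerehabilitation".
- **Analysis.** For the experience objective, Statistical analysis summarises categorical answers as frequencies and proportions and compares Yes with No responses.
- **Second source.** The same section says of the subjective framework: "patients are asked a directed open-ended question on their experience of the call and the telerehabilitation sessions". These answers are grouped into themes.

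**The concern.** If people are asked about the service when they are discharged, and discharge is described as following a good result, then whether a person is asked depends partly on how well treatment went. Someone who withdraws, or who is recalled after one session, has used telerehabilitation and has an experience to report, but reaches no contact at which the article says the structured questions are put.

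Experience is the first objective listed. The article also says the study will determine whether the service is feasible during and after the pandemic, and that findings will go to policymakers. People for whom telephone care did not work are especially informative about feasibility. No later analysis can recover answers that were not collected.

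**Working it through.** **Step 1. Who reaches the stated assessment point?** The documents give no satisfaction, withdrawal or transfer rate, so there is no planned figure to reproduce. The stated routes can be set side by side.

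| Route | Where stated | Structured experience assessment described? |
|---|---|---|
| Discharged at functional goal | Arthroplasty and paediatric Procedures | Yes: abstract; for children also the final consultation |
| Discharged at STarT Back below three | Low back pain Procedures | Yes: abstract |
| High-risk back pain, recalled after session one | Low back pain Procedures | None described |
| Withdrawal at any time | Ethical considerations | None described |
| Child considered for face-to-face care | Paediatric Procedures | Possibly: this sentence directly follows the one on final-consultation feedback |

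The gap is clear in the third and fourth rows and uncertain in the fifth.

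**Step 2. Does the open-ended question close the gap?** The framework that holds it is used before discharge. Arthroplasty follow-up is conducted "by using the subjective assessment framework", low back pain uses an adapted version, and each paediatric follow-up records "the response of the child to the HEP and feedback/concerns from the caregiver, by using the Subjective Assessment Framework". Two things limit its value here:

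- Its answers become themes and are not described as entering the Yes/No proportions.
- The framework questions that are shown (Table 1 and Appendix 4) contain no question about the experience of the call. Appendices 1 and 2, which hold the arthroplasty notes and the low back pain framework, are not shown. When the question is asked therefore cannot be confirmed.

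It reduces the gap without closing it.

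**Step 3. How large could the effect be?** All values here are assumptions. Let *d* be the share never asked, *p* the proportion satisfied among those asked and *q* the proportion satisfied among those not asked.

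- True proportion = (1 − *d*)*p* + *dq*
- Overstatement = *p* − true proportion = *d*(*p* − *q*)
- Limits with no assumption about *q*: from (1 − *d*)*p* (nobody unasked is satisfied) to (1 − *d*)*p* + *d* (all are)

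With *p* = 0.90, *d* = 0.20 and *q* = 0.50: true = 0.80 × 0.90 + 0.20 × 0.50 = 0.82, and overstatement = 0.20 × 0.40 = 0.08.

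| *d* | Overstatement, *q* = 0.90 | *q* = 0.70 | *q* = 0.50 | *q* = 0.30 | Limits on the true proportion |
|---|---|---|---|---|---|
| 0.10 | 0 | 2 points | 4 points | 6 points | 81–91% |
| 0.20 | 0 | 4 points | 8 points | 12 points | 72–92% |
| 0.30 | 0 | 6 points | 12 points | 18 points | 63–93% |
| 0.40 | 0 | 8 points | 16 points | 24 points | 54–94% |

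For *q* between 0.30 and 0.70, a reported 90% would correspond to a true value between 66% (0.60 × 0.90 + 0.40 × 0.30) and 88% (0.90 × 0.90 + 0.10 × 0.70).

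**The case against.** A reader might infer that experience is collected only at discharge. The documents do not support that: the open-ended question belongs to a framework used at earlier sessions. Appendix 4 also asks caregivers what is difficult with the exercises and whether they are coping. This part of the objection stands and narrows the point to the structured assessment.

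Discharge is worded permissively. Patients *can* be discharged on reaching the goal or score, which does not exclude other routes, and the paediatric final consultation depends on the child's condition rather than explicitly on success. That is fair. Selection on a good course is therefore an inference from the only criteria stated, not something the plan declares.

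Children moved to face-to-face care may well be asked. Feedback at the final consultation comes first in the text and the possible switch comes next, so dissatisfied caregivers may be among the respondents. This stands, and the point does not rest on that group. Nor does it rest on patients without data or airtime, since the procedure is built mainly on the therapist telephoning. Therapists' own feedback is not lost when a patient leaves.

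Finally, this is a condensed article, and exit procedures, analysis sets and response-rate reporting often sit in a fuller document. Their absence alone would not be a finding. What remains is a timing that the article does state, in two places, alongside discharge criteria that it also states. Followed as written, the two together tie the structured answers to the patient's course.

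**Conclusion.** The point holds in limited form. The structured experience assessment is timed at discharge or the final consultation, the stated discharge criteria are good results, and no such assessment is described for patients who withdraw or for high-risk back-pain patients recalled after session one. Reported satisfaction *may* be overstated.

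A reader might go further and conclude that it *is* overstated. The documents do not support that. The direction is plausible, because recall follows a high-risk classification and withdrawal may follow dissatisfaction, but the size depends on the share not asked and on their views, and neither is given. The 2 to 24 points in the table illustrate assumed values and are not an estimate; the overstatement is zero if those not asked are equally satisfied. The conclusion also assumes that the unseen Appendices 1 and 2 do not already put structured experience questions to every adult at each session. The change is worth making because it protects the first objective at little cost.

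**What to change.** 1. Put the existing experience questions to everyone who had a first session at one fixed contact, whatever their progress. About 3 months would fit, since the paediatric goal review in Appendix 4 already uses that time.
2. Offer the same questions at withdrawal or transfer to face-to-face care. Answering must be voluntary, because participants may leave without giving a reason.
3. State at which sessions the open-ended experience question is asked.
4. Report results over all who had a first session, with the response rate, the number not asked, and early leavers shown separately.

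This changes only when questions are asked and how answers are reported; treatment, discharge and recall are untouched. The cost is a short extra call for some early leavers, not all of whom will be reached. Reported satisfaction may also come out lower.

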**Discussion:**

Because of the current coronavirus disease 2019 (COVID-19) pandemic, patients are unable to receive traditional face-to-face physiotherapy services. Telerehabilitation offers a suitable alternative to treatment, but the feasibility, outcome and experiences of offering these services in the public health system have not been studied.

**Conclusion:**

This study will determine whether telerehabilitation is a feasible service that can be offered in the COVID-19 pandemic, as well as post-pandemic, to enable physiotherapists to access those patients who are often unable to attend physiotherapy because of transport costs and various other reasons for non-attendance.

**Clinical implications:**

The results of this study may indicate a way of managing patients in situations where face to face therapy cannot be undertaken.

**Protocol identification:**

Pan African Clinical Trial Registry, PACTR202103637993156.

## Introduction

On Thursday, 05 March 2020, the National Institute for Communicable Diseases confirmed the first positive case of coronavirus disease 2019 (COVID-19) in South Africa. This led to the announcement of a National State of Disaster by President Cyril Ramaphosa, and a 21-day lockdown was implemented on 26 March 2020. The National State of Disaster, as well as the 21-day lockdown, had tremendous implications for health professionals in terms of the manner in which services had to be prioritised and delivered. Shortly thereafter, the Department of Public Service and Administration issued Circular 18 of 2020 mandating healthcare institutions to find means to deliver healthcare services to patients by using online platforms rather than visiting physical service points. Gauteng Department of Health employees were encouraged to practise telehealth during the COVID-19 pandemic as a means of ensuring continuity of care whilst simultaneously reducing the risk of infection for patients, caregivers and healthcare professionals. Hence, it necessitated an urgent need to find ways to access the public (existing clients or patients) through the use of telephone and other online means.

Telerehabilitation refers to the mode of delivering rehabilitation services and public health awareness via information and communication technologies to facilitate the diagnosis, consultation, treatment, education, care management and self-management of a patient’s healthcare, whilst the patient is at the originating site and the healthcare provider is at the distant site (Chaet et al. 2017). Terminologies such as telerehabilitation and telephysiotherapy, which are branches of telehealth, are used interchangeably to describe the delivery of rehabilitation services to patients over the telephone or via an email or text message (Keerthi, Chandra & Deepak 2013). Telerehabilitation is thus delivered at a distance with the use of electronic communication and information technologies in the comfort of patients’ homes (Shaw 2009). This method of rehabilitation may be more feasible for the patient and hospital (Kuether et al. 2019) and will improve access for patients facing challenges because of transport and geographical considerations (Peretti et al. 2017). The success of a telerehabilitation session is dependent on the therapist linking the intervention content (cognitive behavioural therapy, education, reminders about self-management) and the type of telerehabilitation delivery (short message service [SMS] or cellular phone apps). Hence, this approach to service delivery provided the solution to the challenges posed by the COVID-19 pandemic.

Historically, telehealth implementation in South Africa was poor because of a lack of awareness and knowledge on the scope of practice (Mars 2011), as well as the Health Professions Council of South Africa (HPCSA) guidelines, which prevented the use of telehealth services by healthcare professionals (HPCSA 2014). Previously as well there had been usage of emails and telephone calls, but this was limited to general follow-up with patients or to serve as reminders for group classes. Whilst literature exists as to the benefits of telerehabilitation (Cason 2009; Kuether et al. 2019; Movahedazarhouligh et al. 2015; Odole et al. 2015; Peretti et al. 2017), there are limited studies that explore the use of telerehabilitation in public health settings in developing countries (Movahedazarhouligh et al. 2015). The potential benefit for telerehabilitation is greater in a developing country, especially in an under-resourced setting (Combi, Pozzani & Pozzi 2016).

As a result of the COVID-19 pandemic, the HPCSA and the South African Society of Physiotherapists (SASP) modified their stance and issued new guidelines on telerehabilitation services (HPCSA 2020; SASP 2020). Additionally, in the guidelines for telerehabilitation provided by the SASP, the use of telerehabilitation in many different fields of physiotherapy was explored, but not elaborated for use in orthopaedic conditions such as arthroplasty and chronic low back pain. Because of the lack of literature on telerehabilitation implementation in a public health context and to answer the challenges posed to the delivery of telerehabilitation services because of the COVID-19 pandemic, this proposal was created to streamline the mode of delivery of telerehabilitation. In addition, it aims to measure the effects of delivery of outpatient physiotherapy services by means of telerehabilitation as well as record the patient’s/caregiver’s and physiotherapist’s experiences.

### Problem statement

As a result of the COVID-19 pandemic, many patients who required outpatient rehabilitation services had not been able to attend the physiotherapy department to access the care they require to manage their conditions and prevent disability. As the pandemic progressed, the risk of contracting COVID-19 for those who attend public health facilities remained high, as the risk of exposure increased. The shift in the guidelines and legislations surrounding the practice of telerehabilitation as of March 2020 permitted its implementation for healthcare professionals in South Africa. Because of the existing gap in literature regarding telerehabilitation in public health context, this study will explore the effectiveness and experiences of telerehabilitation.

### Significance of the study

Because of the implications of social distancing and the responsibility of health professionals to assist in the promotion and protection of the health of the population, the use of online platforms to deliver healthcare services has become an urgent need. This study will help to determine the feasibility of using telerehabilitation to deliver services to orthopaedic, neuromusculoskeletal (NMS) and paediatric patient populations in the public health setting. In addition, this study will also assist in serving as operational research to investigate the long-term feasibility of a telerehabilitation approach in terms of staffing, resources, cost, and access for patients and in the long run serve to reduce the burden of disease in this population group.

### Objectives

The objectives of the study are as follows:

To determine the patient and/or caregiver and physiotherapist experiences in the rollout of telerehabilitation for selected outpatient groups.To determine the effects of telerehabilitation services for patients who have orthopaedic conditions (arthroplasty), NMS conditions (chronic low back pain) and paediatric conditions (cerebral palsy, developmental delay and orthopaedic conditions).

## Methods and design

Purposive sampling will be used for this prospective mixed method study. Patients who have previously attended the outpatient physiotherapy department for the management of their orthopaedic, NMS and paediatric conditions prior to the national lockdown and those who had to have their appointments cancelled will be invited to participate. These patients will be selected as they are long-term patients requiring ongoing physiotherapy to prevent further disability but are not prioritised for face-to-face consultations because of the COVID-19 pandemic. Initially, a pilot study will be conducted to determine the sample size and rule out any errors in the methodology, and thereafter the study will be expanded.

A standard operating procedure (SOP) will be developed for arthroplasty (orthopaedic) and patients with chronic low back pain (NMS), cerebral palsy, developmental delay and acute orthopaedic conditions (paediatrics) with the purpose of providing an outline for therapists to deliver telerehabilitation services effectively and ethically. For each area, a database will be created containing videos and images of relevant interventions related to the specific condition being treated. Exercise prescription will commence from the patients’ current level of function and will be progressed as per the criteria described in the section’s guidelines of management of arthroplasty, chronic low back pain and paediatric patients. A section on general advice and health education will also be included.

Available methods of delivering telerehabilitation services include telephone calls, text messages (SMS or WhatsApp) and emails. Two modes of communication will be used for every participant, and this will be determined by the resources the patient has availed. The participant will initially be contacted via a telephone call, and the concept of telerehabilitation will be explained to them. Informed consent will be obtained from the patient for participation in the research, along with the consent for audio and/or video recordings of the session; therapists are to send or receive video and audio recordings as well as the caregiver to send or receive video and audio recordings should the patient not have a suitable phone. The preferred language of delivery (English or Zulu) will be obtained verbally from the participant prior to proceeding with telerehabilitation services. The mode of delivery of telerehabilitation services will be established at the initial contact. A suitable date and time for each session will be agreed upon between the physiotherapist and the participant. The type of delivery of information and the model of the patient’s phone will guide the extent of information transferred.

The participant and two physiotherapists will be present at each telerehabilitation consultation. Two physiotherapists will be present, as one physiotherapist will provide the telerehabilitation service and the other will record all necessary information, that is, the scribe. The call should therefore be on loudspeaker, in a private office to ensure confidentiality.

Permission will be obtained from the patient to record the session, and it will be an audio recording or video recording depending on how the session is conducted with the patient. The session will be recorded by using a specific app or device. This will be downloaded and stored on Google drive and will be backed up onto an external hard drive. The same will be done for the physiotherapy notes. All will be anonymised and there will be no names or identifying information on the recording.

Consistency and reliability during the proposed telehealth sessions will be ensured by following the telehealth guidelines set out by the SASP during 2020 and the HPCSA in 2014 and 2020. Participants will be asked to provide feedback for the orthopaedics and NMS subgroup and to complete a questionnaire for the paediatric population to provide their perceptions and experiences of telerehabilitation. For all interactions, attempts will be made to communicate with participants in their language of choice.

